## Discussion

The potential for neurocognitive training to prevent or mitigate the effects of cognitive deficits associated with various acute and chronic disease states has been investigated in other patient groups, but PEaPoD is the first study to do so in cardiac surgical patients, a subset of the population at highest risk for the development of postoperative delirium and POCD. Additionally, this novel study focuses on a prehabilitative intervention, whereas the majority of the work in the field focuses on alternative anesthetic and analgesic strategies, postoperative behavioral interventions, or cognitive rehabilitation after the insult has already occurred. Should the concept of perioperative neurocognitive training prove to be feasible through the conduct of this study, it will provide the framework for rigorous and efficient investigation into the technique’s efficacy as a low-risk, patient-led intervention for the prevention of significant perioperative morbidity affecting hundreds of thousands of patients in the USA alone on an annual basis.

Our study’s main limitation is that is not powered to detect a difference in clinical outcomes. Before a rigorous investigation into the efficacy of neurocognitive training in reducing postoperative delirium and POCD can be performed, the feasibility of our intervention in this population needs to be determined. While our sample size is larger than some would consider necessary for evaluating feasibility, it will provide accurate information as to an estimated timeline for a larger study and guide decision making as to whether a multicenter efficacy trial is a logical next step, as well as provide an estimate of effect size which can be used to power larger studies. Another limitation comes in the selection of the MoCA as our instrument for measuring POCD, a condition for which it has yet to be extensively validated. POCD is usually evaluated using an in-depth neuropsychological test battery. The MoCA provides multiple potential advantages over this approach in this setting. First, it is shorter, taking 15–20 min rather than 45–60 min to complete. Second, it is highly sensitive in detecting mild cognitive deficits. Third, it has multiple versions including a telephonic equivalent, minimizing the learning effect on test performance and providing a means for longitudinal comparison over a 6-month study period without the need for additional in-person patient visits. Most importantly, it assesses many of the cognitive areas of interest in the evaluation of the patient with potential POCD including attention, memory, and language.

In addition to these limitations, a potential source of bias in our study is the possibility for our assessors to become unblinded to group assignment throughout the course of a 6-month study period. We have taken many steps to prevent this occurrence and have systems in place to manage unblinding if it does occur. Throughout the course of the study, unblinded investigators will reiterate the importance of maintaining the blind, including detailed conversations both at the time of consent and prior to blinded study interactions (e.g., in-hospital cognitive assessments) on how to avoid potential conversations regarding the use of a mobile device in general. In an effort to maintain consistency, clearly defined roles have been delineated within the research group, with two unblinded team members solely responsible for monitoring adherence and technical support who are never involved in the assessment process. If an assessor does become unblinded, an alternate blinded team member trained in administering the CAM and MoCA is made available. If an alternate blinded team member is not available, the assessment is not performed and will be treated as missing data.

To summarize, elderly patients undergoing cardiac surgery have the highest incidence of postoperative delirium and POCD, which places them at an elevated risk for significantly higher perioperative morbidity and long-lasting detrimental effects on cognition. Neurocognitive training has been shown in preliminary studies to be effective in improving cognitive performance in the areas thought to be affected in the postoperative period. PEaPoD will be the first study to investigate the use of perioperative neurocognitive training in this high-risk patient population. Through the performance of this study, valuable information will be obtained that will guide future studies that are well designed to examine the technique’s efficacy in preventing postoperative delirium and POCD.

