## Methods and design

### Study design

The Prevention of Early Postoperative Decline (PEaPoD) study is a randomized, controlled, single-center, assessor-blinded clinical trial of eligible older adult cardiac surgical patients. Subjects will be randomized in a 1:1 allocation to either perioperative neurocognitive training or usual care control. The primary outcome of feasibility will be determined based on enrollment and protocol adherence. Secondary outcomes, including the incidence of postoperative delirium and POCD, will be evaluated using the Confusion Assessment Method (CAM) and the Montreal Cognitive Assessment (MoCA) respectively. Additionally, patients will be followed until 6 months postoperatively and evaluated via a telephonic MoCA (t-MoCA) to assess the presence of long-term POCD and to map the trajectory of return to baseline cognitive function. A study schema is provided in Fig. 1. Our study protocol was written according to the principles outlined in the Standard Protocol Items: Recommendations for Interventional Trials (SPIRIT) checklist (Fig. 2, Additional file 1) [20].

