### Study intervention: neurocognitive training

Patients will be randomized in a 1:1 allocation via a concealed block scheme to either intervention or control using the Research Electronic Data Capture (REDCap) randomization feature. Patients randomized to the intervention group will be asked to complete two 15-min neurocognitive training sessions per day, from the day of enrollment until 4 weeks after their day of surgery including the immediate postoperative in-hospital period. Our inclusion criteria were designed so that study participants with at least 10 days of lead-in time could then complete at least 5 h of training before surgery, with the understanding that there may be unequal durations of gameplay based on scheduling patterns among patients. The training instrument used in this study, Lumosity, was created by Lumos Labs Inc., San Francisco, CA, USA, as a web-based and mobile platform designed to improve performance in specific cognitive abilities through interactive gameplay. As part of a customized training program tailored towards cognitive abilities thought to be deficient in the postoperative period, patients in the intervention arm will train in each of the following categories per session: memory, attention, problem solving, flexibility, and processing speed. Participants in the intervention arm will be given a study iPad that is WiFi enabled and locked to the Lumosity program. Adherence to the study protocol will be quantified using automated gameplay data received from Lumos Labs. Unblinded study members will be responsible for providing technical support to participants as needed and for periodic checks on adherence between in-person assessments.

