##### Data analysis

Patients will be prospectively randomized using 1:1 block randomization. Analyses will be conducted using SAS version 9.4 (SAS Institute Inc., Cary, NC, USA) or later. Descriptive statistics of the data will be performed. Continuous data will be represented using mean (± standard deviation) or median (interquartile range) for variables not normally distributed and compared using parametric or non-parametric tests as appropriate. Categorical data will be presented as frequencies and proportions and compared using a chi-square or Fisher’s Exact test.

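### Unblinded staff talk with patients at consent, before assignment, in a single-centre block-randomised trial, which creates an avoidable risk that the next assignment is partly predictable

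*Protocol article*

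**What the plan says.** The Study design section describes a "randomized, controlled, single-center, assessor-blinded clinical trial of eligible older adult cardiac surgical patients". Under Study intervention, patients are "randomized in a 1:1 allocation via a concealed block scheme to either intervention or control using the Research Electronic Data Capture (REDCap) randomization feature". Data analysis repeats the block method: "Patients will be prospectively randomized using 1:1 block randomization". Neither section gives the block size.

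The Discussion, on protecting the assessor blind, says that "unblinded investigators will reiterate the importance of maintaining the blind, including detailed conversations both at the time of consent" and again before blinded assessments. It gives the subject of these talks as "on how to avoid potential conversations regarding the use of a mobile device in general". The next sentence describes "two unblinded team members solely responsible for monitoring adherence and technical support who are never involved in the assessment process".

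The day-to-day duties of these staff are under Study intervention: "Unblinded study members will be responsible for providing technical support to participants as needed and for periodic checks on adherence".

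**The concern.** Concealment at enrolment needs more than a hidden list. In an open-treatment trial with blocked allocation at one site, someone who knows the earlier assignments can often tell which arm is due next. The usual safeguard is to keep such people away from patients until the assignment is made. The Discussion does the opposite for one task, because it puts unblinded investigators with the patient at consent.

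A person who expects the next patient to train, or to be a control, may encourage one patient more than another without meaning to. That can make the arms differ in baseline risk. The comparisons exposed are the secondary ones, delirium and POCD. They matter beyond this trial because the Discussion intends the effect estimate to be used to power larger studies. With 20 patients per arm, one selectively enrolled patient whose outcome differs moves an arm's proportion by 1/20 = 5 percentage points.

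**Working it through.** **The plan's own figure.** The Sample size calculation section gives 20 randomised patients per group plus five for screen failures and withdrawals: 20 + 20 + 5 = 45. This reproduces. The calculations below use the 40 randomised patients.

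**Does the consent contact come before assignment?** Under Dropout criteria, the baseline MoCA follows consent, and a score below 10 leads to withdrawal. The Sample size calculation section adds five patients, partly for failures of that screen, on top of the 20 randomised per group. The natural reading is consent, then screen, then assignment.

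**Can the unblinded members know earlier allocations?** The article does not say so; it follows from their duties. Only the training arm receives an iPad and produces gameplay data, so staff who support the device and check adherence learn who trains. At one centre, the other randomised patients are the controls.

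**How predictable would the next assignment be?** Block size is not reported, so it is assumed over a range. For a fixed 1:1 block of size 2m, with size and all past assignments known:

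- share of assignments certain in advance = 1/(m + 1)
- share guessed correctly when always naming the arm with fewer patients so far in the block = [m + (4^m / C(2m, m) − 1)/2] / (2m)

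Worked for m = 2: certain = 1/3 = 0.333; correct = [2 + (16/6 − 1)/2]/4 = 2.833/4 = 0.708.

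| Block size | Certain | Certain among 40 | Guessed correctly |
|---|---|---|---|
| 2 | 50% | 20.0 | 75% |
| 4 | 33% | 13.3 | 71% |
| 6 | 25% | 10.0 | 68% |
| 8 | 20% | 8.0 | 67% |
| 10 | 17% | 6.7 | 65% |
| 20 | 9% | 3.6 | 62% |
| 40 (one block) | 5% | 1.9 | 59% |

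**If block sizes vary and the guesser does not know them.** This was simulated with 40 assignments and 20,000 repeats, guessing the arm with fewer patients so far and tossing a coin on ties. Correct guesses were 72% for sizes 2 or 4, 69% for 4 or 6, 70% for 2, 4 or 6, and 68% for 4, 6 or 8.

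Chance is 50%, or 20 of 40. For fixed blocks of 4 to 8, the guesser expects 40 × 0.708 = 28.3 down to 40 × 0.666 = 26.6 correct. Varying the sizes removes most of the certainty about single assignments but leaves the overall guess rate about the same.

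**Role statements side by side.** One sentence of the Discussion has unblinded investigators talking with patients at consent. The next confines two unblinded members to adherence monitoring and technical support. Either those two act outside their stated role, or there are further unblinded investigators whose role is not described. Neither reading fits comfortably with the concealment stated under Study intervention.

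**The case against.** The case against has real weight.

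- **Purpose of the talks.** Their stated subject is protecting the assessor blind, not persuading patients to join. No section says that unblinded staff select, approach or consent patients. The words limiting the two members' role, read literally, point away from recruitment. The screen after consent is done by blinded investigators against a fixed score.
- **Timing.** Training starts on the day of enrolment, so the time of consent could loosely mean the whole visit, including the part after assignment.
- **Unstated facts.** Full knowledge of past allocations is inferred. Block size, and whether it varies, are details an article may properly leave out, and their absence is not a fault.
- **Generality.** A guess rate above chance is a property of blocked allocation with open treatment, not of this plan alone.

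All of this limits the point but does not remove it. Unintended encouragement needs only contact near the decision, and the text places that contact there. The general property becomes a risk only when people who know the tally meet patients before assignment, and that is the part this plan fixes by choice.

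Two stronger readings are tempting. A reader might infer that the stated concealment is defeated. The documents do not support this: the list stays hidden in REDCap, and nothing shows that anyone predicts or acts on assignments. A reader might also infer that the primary recruitment outcome is distorted. That criterion, under Primary outcome, is enrolment of at least 50% of eligible patients overall. It is not compared between arms, so guessing the arm gives it no clear direction of bias.

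**Conclusion.** The point holds as an avoidable risk, not as a demonstrated failure. The plan puts unblinded staff, who are in a position to know earlier allocations, in contact with patients before assignment in a single-centre blocked trial. This sits badly with its own statements on concealment and on role limits.

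For blocks of 2 to 8, fixed or varying, a well-informed guess would be right about 67% to 75% of the time; even a single block of 40 gives 59%. These figures are upper bounds in practice. They assume that every past assignment is known and, for the fixed blocks, that the size is known too. How far any guess would translate into selective enrolment cannot be computed from the article.

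The exposure is to the secondary delirium and POCD comparisons and to the effect estimate intended for later trials. The Discussion acknowledges that the trial is not powered for those outcomes, but lack of power does not protect an estimate from bias. The pooled recruitment rate is not affected in any clear way.

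**What to change.** Amend the Discussion paragraph on unblinding so that all contact before randomisation, including the consent discussion, is held by existing team members without access to earlier allocations. Unblinded members would first meet the patient, and give the advice on keeping the blind, after the REDCap assignment. Reconcile the two role sentences at the same time, so that it is clear whether anyone beyond the two named roles is unblinded.

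No extra staff are needed: blinded investigators already see each patient on the day of enrolment for the baseline MoCA, and before assignment the patient has no allocation to reveal. The trial is ongoing and the Study registration section provides for amendments through the IRB. The cost is a small loss of convenience, because the device walk-through and the talk on keeping the blind can no longer be combined with the consent discussion and must follow randomisation.

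A request for varying block sizes is not part of this fix. The scheme may already use them, and the figures above show that they barely lower the guess rate. Separating the roles is what removes the risk.

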## Abbreviations

ACTIVE: Advanced Cognitive Training for Independent and Vital Elderly
BIDMC: Beth Israel Deaconess Medical Center
CAM: Confusion Assessment Method
CARE: Center for Anesthesia Research Excellence
CONSORT: Consolidated Standards of Reporting Trials
CPB: Cardiopulmonary bypass
HELP: Hospital Elder Life Program
ICU: Intensive care unit
IRB: Institutional Review Board
MoCA: Montreal Cognitive Assessment
PEaPoD: Prevention of Early Postoperative Decline
POCD: Postoperative cognitive decline
REDCap: Research Electronic Data Capture
SPIRIT: Standard Protocol Items: Recommendations for Interventional Trials
t-MoCA: Telephonic Montreal Cognitive Assessment
